### Participant withdrawal

If the participant decides to withdraw from the trial they can 1) participate in the baseline interview and then withdrawal from the treatment but participate in the follow-up interviews; 2) participate in the baseline interview and then withdrawal from the treatment and not participate in the follow-up interviews 3) withdraw from the whole trial so that all data about them are deleted.

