## Analysis

### Power and sample size

We are planning a trial of the continuous response variable, GAF-F, from independent control and experimental participants with one control per experimental participant. A previous study involving psycho-education in a Danish community mental health centre showed that response within each participant group was normally distributed with a standard deviation of 15 [38]. In the few previous studies using IMR or elements of IMR the effectiveness has been assessed by using the total GAF score showing a difference of 6-10 points [21,39]. Based on this knowledge we will conservatively estimate the true difference in the experimental and control group means to be 6 points on the GAF-F score. Using this estimation will require a total of 200 participants to reject the null hypothesis that the population means of the experimental and control groups are equal with probability (power) 0.8. The type I error probability associated with this test of the null hypothesis is 0.05. The power and sample size calculations have been made using the PS Power and Sample Size Calculations program version 3.0.34 [40].

The power of some the secondary measures has also been estimated with a total number of 200 participants. This showed that a sample size of 200 participants is sufficient to show a relevant effect size in PSP, PANSS and the IMR Scale corresponding to similar studies, see table 2. The remaining secondary measures have not been tested due to the fact that similar trials with these outcomes could not be obtained. Thus, the results of these analyses should be interpreted with caution, and the analyses should be considered as exploratory.

**Table 2 T2:** Power calculations of PSP, PANSS and IMR Scale

Measure	The level of significance	Power	St. deviation in a similar study	Effect size in a similar study	Minimum sample size	Reference
PSP	0,05	0,8	14	7	128	*Nasrallah et al. 2008 *[40]

PANSS	0,05	0,8	11	5	154	*Fowler et al. 2009 *[41]

IMR scale	0,05	0,8	0,5	0,41	48	*Hasson-Ohayon et al. 2007*[17]

Note: PSP: Personal and Social Performance; PANSS: Positive and Negative Syndrome Scale; IMR Scale: Illness Management and Recovery Scale.

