## Data analysis

The analysis will be performed by using the IBM SPSS Statistics version 19 for Windows. The data analysis will be based on the principle of intention-to-treat. The significance level for the analysis of the primary outcome and the secondary outcome will be 0.05.

Demographic variables will be listed in a table. The primary outcome measure is the continuous measurement GAF-F. The primary analysis of effectiveness will compare GAF-F at 9 months. The secondary analysis will compare effectiveness of the secondary outcome measures at 9 months and GAF-F and the secondary outcomes at 21 months. The analysis of differences between groups will be conducted using t-tests and analysis of the variances will be conducted using ANOVA. Repeated measures techniques may also be applied. Dichotomous outcome assessments will be analysed using logistic regression and paired dichotomous outcomes will be analysed using McNemar tests, or using logistic regression with random effects. Missing data is a potential source of bias and therefore the operation of multiple imputations will be used to address the issue of missing values. An analysis of the drop-out will be conducted to validate the complete case analyses.

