## Discussion

The IMR trial is a randomised clinical trial to evaluate the effectiveness of the IMR-program for people diagnosed with schizophrenia and bipolar disorder in according to their level of functioning.

In this design of testing the IMR program an important factor is to insure the fidelity to the IMR program curriculum, so that the IMR program is the taught the same way, using the same slides and same topic areas across the participating community mental health centres. A strength of this trial is therefore that all IMR facilitators go through a specific course of education prior to the intervention, have profound supervision during the intervention and that we test the fidelity using the IMR fidelity scale throughout the course of each IMR group.

Another strength in the design of this trial is that a solid sample size calculation has been made, so we will be able to perform a data analysis with good strength according to the primary outcome, GAF-F. Besides this we have estimated the power of some the secondary measures with a total number of 200 participants. This showed that a sample size of 200 participants is sufficient to show a relevant effect size in the secondary outcome measurements PSP, PANSS and the IMR Scale which will strengthen the results in these aspects. Furthermore, the risk of selection bias related to allocation sequence generation and concealment is low, as the randomisation is performed centrally according to a computer-generated allocation sequence generation. The fact that the assessor of the primary outcome is blinded and that intention-to-treat analysis are going to be used as a statistically approach in the data analyses are also strengthening the design of this trial.

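### The 200 participants needed for 80% power are also the 200 enrolled, so the stated power holds only with almost no loss by 9 months

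*Protocol article*

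**What the plan says.** All references are to the Protocol article.

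- **Power and sample size.** The authors "conservatively estimate the true difference in the experimental and control group means to be 6 points on the GAF-F score", with SD 15 and one control per experimental participant. The conclusion is: "Using this estimation will require a total of 200 participants to reject the null hypothesis that the population means" are equal, with power 0.8. On the error rate: "The type I error probability associated with this test of the null hypothesis is 0.05".
- **Abstract and Methods/Design.** The same 200 is the number of participants in the trial.
- **Participant withdrawal.** Three routes are listed. The first keeps the person in the follow-up interviews. The second is "withdrawal from the treatment and not participate in the follow-up interviews". The third deletes all of the person's data.
- **Data analysis.** The primary comparison is GAF-F at 9 months, and group differences are tested with t-tests. Repeated measures techniques are only a possibility. The section says "Missing data is a potential source of bias" and plans multiple imputation and an analysis of drop-out.
- **Discussion.** Listed as a strength of the trial: "a solid sample size calculation has been made, so we will be able to perform a data analysis with good strength" for GAF-F.

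**The concern.** The number that the power calculation requires and the number enrolled are both printed, and they are equal. The primary outcome comes from an interview, so a participant who leaves by the second or third withdrawal route has no 9-month GAF-F. Such participants are foreseen in the withdrawal section and again in the missing-data plan, but they do not enter the sample size.

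If some are lost, the primary t-test has less than the stated power for the difference it was designed to detect. A null result could then be read as coming from a trial with 80% power for 6 points when its power was lower. This bears on the trial's own rationale, because the Background counts the power of earlier trials among their limitations.

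**Working it through.** **Inputs from Power and sample size.** Difference 6; SD 15; alpha 0.05; power 0.8; 1:1 allocation. Sidedness is not stated. Two-sided is inferred because the aim is to "reject the null hypothesis that the population means of the experimental and control groups are equal", and because a one-sided test would need only 78 per arm (156 in total), which does not match 200.

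**Reproducing the plan's figure.** Standardised difference = 6/15 = 0.4.

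- Normal approximation: n per arm = 2 × (15/6)² × (1.960 + 0.842)² = 2 × 6.25 × 7.85 ≈ 98.1, so 99 per arm, 198 in total.
- Two-sample t-test: 99.08 per arm, so 100 per arm, 200 in total.
- t-test power is 0.804 at 100 per arm and 0.7997 at 99 per arm.

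The plan's 200 is reproduced. It is the number with an observed outcome, and the margin is about one participant per arm.

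**Power if some are not assessed.** The article gives no loss rate, so a range is assumed, equal in both arms. Number assessed per arm = 100 × (1 − loss). Power is from the two-sided t-test at standardised difference 0.4. The last column is the difference detectable with 80% power at SD 15.

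| Assumed loss | Assessed per arm | Power for 6 points | Detectable difference |
|---|---|---|---|
| 0% | 100 | 0.804 | 5.97 |
| 5% | 95 | 0.783 | 6.13 |
| 10% | 90 | 0.761 | 6.30 |
| 15% | 85 | 0.737 | 6.48 |
| 20% | 80 | 0.710 | 6.69 |
| 25% | 75 | 0.682 | 6.91 |

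At 20% loss the type II error is 1 − 0.71 = 0.29, against the planned 0.20.

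**What baseline adjustment could recover.** If baseline GAF-F correlates r with the 9-month score, the residual SD is 15 × √(1 − r²). Power of 80% for 6 points is restored when √(1 − r²) = 6 / (detectable difference without adjustment).

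- 10% loss: 6/6.30 = 0.953, so r ≈ 0.30.
- 20% loss: 6/6.69 = 0.897, so r ≈ 0.44. At r = 0.45 the residual SD is 13.4 and power is 0.804.
- With r = 0.5, power at 20% loss is 0.83; with r = 0.3 it is 0.75.

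The article states no r, so these values too are assumptions.

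**The case against.** **No figure is wrong, and an attrition assumption may be in a fuller document.** The first half stands: the arithmetic for 200 is correct, and a reader who inferred a miscalculated sample size would be mistaken. The second half carries less weight. The point does not rest on silence about a detail, since the article prints the required and enrolled numbers and they coincide. A retention assumption stated elsewhere could not make fewer than 200 assessed participants deliver the power computed for 200.

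**The size depends on an assumed loss.** This stands. At 5 to 10% loss, power is 78 to 76% and the detectable difference is at most 6.3 points, a small shift. A reader might infer that the trial is seriously underpowered. The article does not support that, because it gives no loss rate and its first withdrawal route keeps people who stop treatment in the follow-up interviews.

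**Six points is the bottom of the cited 6 to 10 range.** At 80 per arm the t-test has about 83% power for 7 points and 92% for 8. This helps only partly: the Background makes 6 points the hypothesis, and the cited range is for total GAF rather than GAF-F.

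**Imputation and baseline data can make up the loss.** In part they can. GAF-F is measured at baseline, and imputation recovers information as far as observed data predict the missing score. It would be too strong to say that imputation recovers nothing. But the article offers imputation as a remedy for bias, it cannot help where a participant's data have been deleted, and the named test is the t-test. The sample size claims no gain from either source.

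**Group delivery.** A reader might also infer a further loss of power because IMR is given in groups of 10. The article gives no intraclass correlation, so no figure can be put on that here and none is part of this point.

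**Conclusion.** The concern holds in conditional form. The stated power of 0.8 for 6 points requires essentially all 200 participants to have a 9-month GAF-F, while the same article provides for participants who will not. For the named t-test, power is about 76% at 10% loss and 71% at 20%, with detectable differences of 6.3 and 6.7 points. These figures rest on the article's SD and difference, a two-sided test, equal loss in the arms, analysis of observed scores without adjustment, and loss rates that are assumed. The shortfall brings no bias into the estimate, and the confidence interval will show the precision achieved. What needs correcting is the power statement and the Discussion's unqualified reliance on it.

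**What to change.** Choose one of two restatements; neither needs more patients.

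1. State the expected loss at 9 months and the power at the number then assessed. For example: with 20% loss (80 per arm), the t-test has 71% power for 6 points and 80% power for 6.7 points.
2. Prespecify a baseline-adjusted analysis of 9-month GAF-F as primary, and give the power under a stated and justified correlation. At 20% loss, r of about 0.45 restores 80% power for 6 points.

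In either case, qualify the Discussion's statement about the sample size so that it refers to the restated figure. The first option costs a less favourable power figure. The second costs a firm commitment to the adjusted analysis before the data are seen, and a source for r.

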## Data analysis

The analysis will be performed by using the IBM SPSS Statistics version 19 for Windows. The data analysis will be based on the principle of intention-to-treat. The significance level for the analysis of the primary outcome and the secondary outcome will be 0.05.

Demographic variables will be listed in a table. The primary outcome measure is the continuous measurement GAF-F. The primary analysis of effectiveness will compare GAF-F at 9 months. The secondary analysis will compare effectiveness of the secondary outcome measures at 9 months and GAF-F and the secondary outcomes at 21 months. The analysis of differences between groups will be conducted using t-tests and analysis of the variances will be conducted using ANOVA. Repeated measures techniques may also be applied. Dichotomous outcome assessments will be analysed using logistic regression and paired dichotomous outcomes will be analysed using McNemar tests, or using logistic regression with random effects. Missing data is a potential source of bias and therefore the operation of multiple imputations will be used to address the issue of missing values. An analysis of the drop-out will be conducted to validate the complete case analyses.

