### Recruitment and randomisation

Patients will be recruited from two community mental health centres in the Capital Region of Denmark: Frederiksberg-Vanløse and Ballerup-Egedal-Herlev, respectively. Each potential participant is interviewed with the diagnostic tool Present State Examination by a psychiatrist or a trained psychologist to evaluate whether the patient meets the criteria of diagnosis. After informed consent is obtained for each eligible patient the baseline assessments will be conducted. After baseline assessments the participants will be randomly allocated to either IMR or continue with treatment as usual. To secure concealment of the allocation sequence the randomisation will be central and telephone-based through The Copenhagen Trial Unit. The allocation sequence will be computer-generated, using permuted blocks of a varying block size with equal allocation to the two arms. The allocation sequence is stratified by diagnosis and community mental health centre.

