### Primary and secondary outcome measures

The primary outcome of the trial is overall functioning measured by Global Assessment of Function (GAF-F) post-intervention - after nine months. The GAF scale [23] can be divided into two scales GAF-F and GAF-S (one that focuses on functioning and one that focuses on symptoms) [24]. In this trial the focus of the primary outcome is functioning which is why the GAF-F scale is used. Information about the participant's level of functioning will be obtained from interviews with participants at baseline and follow-up.

The secondary outcomes include level of symptoms, social functioning, personal recovery experience and hope, substance abuse, use of services and suicide attempts. This information is obtained through an interview with an assessor blind to the allocation. The participant fill in questionnaires about their personal recovery and hope, the primary care provider (not blinded to the allocation) fill in a questionnaire about substance abuse, adverse events, and suicide attempts. Information about service use is obtained trough the hospital records. The measurements are chosen according to a well-known distinction between clinical recovery and personal recovery [25,26]. Clinical recovery refers to the absence of symptoms, an improvement in functioning and prolonged remission. Personal recovery refers to living a fulfilling and hopeful life even with limitations caused by illness. In this trial we have divided the assessments of recovery in accordance with these two perspectives.

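### The 9-month GAF-F comparison names t-tests and ANOVA without a covariate, so baseline GAF-F, collected before randomisation, is not assigned to the primary analysis: valid, but less precise than it could be at no cost

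*Protocol article*

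**What the plan says.** The Data analysis section sets the primary comparison: "The primary analysis of effectiveness will compare GAF-F at 9 months". The method follows a little later, for all outcomes together: "The analysis of differences between groups will be conducted using t-tests and analysis of the variances will be conducted using ANOVA". It adds: "Repeated measures techniques may also be applied". That last sentence is permissive, is not tied to the primary outcome and does not say how baseline would enter. Analysis of covariance is not mentioned.

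The baseline value is available. Under Primary and secondary outcome measures: "Information about the participant's level of functioning will be obtained from interviews with participants at baseline and follow-up". Table 1 lists GAF-F at baseline, 9 and 21 months, and the Blinding section says that a single assessor does the ratings. On timing, Recruitment and randomisation states: "After baseline assessments the participants will be randomly allocated to either IMR or continue with treatment as usual". On balance: "The allocation sequence is stratified by diagnosis and community mental health centre". Baseline GAF-F is not a stratification factor.

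Power and sample size treats the primary outcome as a plain comparison of two means. It expects a difference of 6 points and takes from a previous study that "response within each participant group was normally distributed with a standard deviation of 15". With a type I error of 0.05 and power of 0.8 it arrives at 200 participants.

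**The concern.** A pre-randomisation measurement of the outcome itself is a legitimate covariate and is usually worth using. If it predicts the 9-month score, adjusting for it removes part of the residual variance. It also corrects the estimate for whatever baseline difference chance has produced between the arms. The methods named in the plan do neither. With two arms and no covariate, one-way ANOVA is the t-test in another form (F = t²), so naming both adds nothing.

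What is at stake is efficiency in a trial sized at 80% power with no reserve, and how the result will read if the arms happen to differ at baseline. Without a pre-specified adjustment, a visible imbalance invites one chosen after the data are seen. The optional repeated measures sentence leaves room for that.

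The same applies to the other scales that Table 1 lists with a baseline value: GAF-S, PSP, PANSS, HAM-D6, YMRS, both versions of the IMR Scale, MHRM, the hope scale and the satisfaction questionnaire.

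**Working it through.** **Inputs from the document (Power and sample size):** difference 6, SD 15, alpha 0.05, power 0.80, allocation 1:1, total 200.

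**Assumptions, not in the document:** correlation r between baseline and 9-month GAF-F, taken from 0.3 to 0.7; baseline SD equal to 15; independent patients; complete follow-up.

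**1. The plan's own figure.** Per arm, n = 2 × SD² × (z₀.₉₇₅ + z₀.₈₀)² / difference² = 2 × 225 × (1.960 + 0.842)² / 36 = 98.1, so 99 per arm and 198 in total. The exact t-test calculation gives 99.1, so 100 per arm and 200 in total. The one-sided version gives 156 and does not match. The stated 200 is therefore a two-sided, unadjusted two-sample comparison, and it is correct. At 100 per arm, power is 0.807 by normal approximation and 0.804 by exact t-test.

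**2. With baseline adjustment.** Residual SD = 15 × √(1 − r²), and the standard error of the arm difference = residual SD × √(2/100). The single degree of freedom spent on the covariate is negligible at this size. The r = 0 row is the unadjusted comparison.

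| r | 1 − r² | Residual SD | SE of difference | Power, 100 per arm (normal approx.) | Total N for 80% power (normal approx.) |
|---|---|---|---|---|---|
| 0 | 1.00 | 15.0 | 2.12 | 0.807 | 198 |
| 0.3 | 0.91 | 14.3 | 2.02 | 0.843 | 180 |
| 0.5 | 0.75 | 13.0 | 1.84 | 0.904 | 148 |
| 0.6 | 0.64 | 12.0 | 1.70 | 0.942 | 126 |
| 0.7 | 0.51 | 10.7 | 1.51 | 0.977 | 102 |

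By exact t-test the powers at r = 0, 0.3, 0.5 and 0.6 are 0.804, 0.839, 0.901 and 0.940. As extra patients, the gain is 1/(1 − r²): 1/0.91 = 1.10, 1/0.75 = 1.33 and 1/0.64 = 1.56. That is 10%, 33% or 56% more participants at r = 0.3, 0.5 or 0.6.

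**3. Chance baseline imbalance.** With baseline SD 15 and 100 per arm, the baseline difference has SE 15 × √(2/100) = 2.12, so 95% of trials fall within about ±1.96 × 2.12 = ±4.2 points. The part that reaches the unadjusted 9-month difference is imbalance × slope. With equal SDs at both times the slope is r. At the 95% limit the shift is 4.16 × 0.3 = 1.2 points, 4.16 × 0.5 = 2.1 points or 4.16 × 0.7 = 2.9 points.

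**4. Whether the optional repeated measures route closes the gap.** With baseline and 9 months as the two times, the arm-by-time test of repeated measures ANOVA is a test of change scores, with SD 15 × √(2(1 − r)). This is 17.7 at r = 0.3, 15.0 at r = 0.5 and 13.4 at r = 0.6. It is worse than the plain t-test below r = 0.5, equal to it at 0.5, and still behind the residual SD of 12.0 from covariate adjustment at 0.6. The route does not secure the gain unless the model is specified.

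**The case against.** The strongest reply is that nothing here is wrong. A two-sample comparison of 9-month scores in a randomised trial is unbiased over randomisation and controls the type I error, and its standard error already reflects chance baseline differences. The sizing and the named test agree. That stands. A reader might infer from this point that the primary test is invalid or that 200 is the wrong number. The document supports neither.

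Second, the article does not say that the primary analysis must be unadjusted. It lists methods for all outcomes together, permits repeated measures techniques, and mentions covariates among the items recorded in the case record form (Monitoring for participant compliance). That also stands in part: it would be too strong to say that the plan rules baseline out. But neither sentence assigns baseline GAF-F to the primary comparison, and the methods the article does name carry no covariate. A separate analysis plan could settle this. The point rests on what the article itself states.

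Third, a reader might infer that a baseline imbalance passes in full into the effect estimate. It does not: it passes in proportion to the slope, as step 3 shows. Stratification by diagnosis and centre gives some prognostic balance, but it does not directly balance GAF-F. The Discussion itself argues that the two diagnoses have similar GAF levels, so stratifying on diagnosis may do little for this variable.

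Fourth, the size of the gain rests on r, which the document does not give. At r = 0.3 the gain is modest, 0.80 to 0.84. That is fair, and it is why a range is shown.

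**Conclusion.** The point holds as a matter of efficiency, not of validity. The named between-group methods leave baseline GAF-F unused for the primary outcome. The t-test remains valid and 200 is correct for it. Adjustment would raise power at 100 per arm from 0.80 to between 0.84 and 0.94 for r from 0.3 to 0.6. It would also correct the estimate for a chance baseline difference that, at its 95% limit, moves the unadjusted result by about 2.1 points at r = 0.5.

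These figures assume r, a baseline SD of 15, independent patients and complete follow-up. The document gives no dropout rate and plans multiple imputation, so no figure for power after losses is claimed. This is a free improvement: worth making, but the trial is not unsound without it.

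**What to change.** Name one primary analysis in the Data analysis section: a linear model (ANCOVA) of 9-month GAF-F on arm, baseline GAF-F, and the stratification factors diagnosis and centre. Put the same terms in the multiple imputation model so that the two are compatible.

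Use the same form for every other scale with a baseline value, and for the 21-month comparisons. Keep the unadjusted t-test as a sensitivity analysis only, and remove the open-ended repeated measures option for the primary endpoint.

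The cost is a change of wording. The baseline data are already scheduled, the sample size stays at 200, and no visits or patients are added.

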**Figure 1 F1:**
[figure not shown]
**The theoretical foundation for Illness Management and Recovery**. The trans-theoretical model and the stress-vulnerability model are the theoretical underpinning of the IMR program.

The core values of IMR are hope, personal choice, collaboration, respect, and recognizing people as experts in their own experience of mental illness. First and foremost, the process of teaching Illness Management and Recovery involves conveying a message of hope and optimism, so that people with mental illness believe that they can reach their own goals and begin a progress of recovery. Non-controlled studies of IMR have provided some support for the effectiveness and feasibility of the program [12-14]. The effectiveness has been tested in a few randomised trials with various settings [15-18] and these trials indicate that IMR in group level can be implemented with a good effect and a high fidelity to the program curriculum [19,20]. Due to methodological limitations in the previous trials regarding the blinding process, follow-up assessments and the power of the sample size further trials are crucial to prove the effect.

In the present IMR trial, the following alternative hypotheses will be tested: Patients in the IMR program will have improved at least 6 points on the Global Assessment of Function scale (GAF-F) compared with patients receiving treatment as usual at follow-up 9 months after baseline. Furthermore, the participants in the IMR program will show a greater improvement after 9 months in relation to symptoms, drug/alcohol addiction, relapse, rehospitalisation and treatment, knowledge about their mental disease, coping strategies, recovery and hope. Moreover the difference between the intervention groups will be sustained 21 months after baseline.

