### Clinical recovery

All outcome measures to assess clinical recovery are continuous scales. The overall level of symptoms is assessed by the subscale of symptoms of the global measurement Global Assessment of Function - Symptoms (GAF-S) [24]. The Positive and Negative Syndrome Scale (PANSS) [27] assesses the level of an severity of positive and negative symptoms as well as the general psychopathology. This scale is primary developed to measure symptoms of people diagnosed with schizophrenia but can be useful to people diagnosed with bipolar disorder as well [28]. The scale is a 7-point rating instrument that consists of 30 items.

Hamilton Rating Scale for Depression scale assesses the level of symptoms of depression. In this trial we use the version of the scale that includes 6 items referred to as Ham D_6 _[29]which is covering the core symptoms of depression.

Young Mania Rating Scale (YMRS) [29,30] is an instrument developed to rate severity of manic episodes. The YMRS consists of 11 items and a severity rating is assigned to each rating.

Personal and Social Performance (PSP) [31] is a scale developed from the Social and Occupational Functional Assessment Scale (SOFAS) to assess psychiatric patients level of functioning [32]. The scale assesses four domains of social functioning: socially useful activities, personal and social relationships, self-care and disturbing and aggressive behaviour. Besides giving more detailed and varied information about the participants' level of function, the PSP scale is used to secure the reliability of the GAF score.

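### For paired dichotomous outcomes the plan allows a McNemar test, which measures change within patients and, if chosen, leaves those secondary outcomes without an IMR versus treatment-as-usual comparison

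*Protocol article*

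**What the plan says.** The Data analysis section of the protocol article deals with binary outcomes in one sentence of two parts. The first part reads "Dichotomous outcome assessments will be analysed using logistic regression". The second reads "paired dichotomous outcomes will be analysed using McNemar tests, or using logistic regression with random effects". It does not say which outcomes count as paired, what forms the pair, or how to choose between the two methods.

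The same section sets the purpose of the secondary analysis: "The secondary analysis will compare effectiveness of the secondary outcome measures at 9 months and GAF-F and the secondary outcomes at 21 months". The matching hypothesis, in the Background, is that "the participants in the IMR program will show a greater improvement after 9 months" on a list that includes drug and alcohol addiction. Both call for a contrast between arms.

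On design, Power and sample size describes responses "from independent control and experimental participants with one control per experimental participant", and Recruitment and randomisation describes individual allocation "using permuted blocks of a varying block size with equal allocation to the two arms". On outcomes, Clinical recovery states that "All outcome measures to assess clinical recovery are continuous scales". Primary and secondary outcome measures adds that "the primary care provider (not blinded to the allocation) fill in a questionnaire about substance abuse, adverse events, and suicide attempts". Table 1 records alcohol and drug consumption, suicide attempts and employment at baseline, 9 months and 21 months.

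**The concern.** The two methods joined by the word *or* answer different questions. A McNemar test uses only the patients whose status changed and asks whether changes in one direction outnumber those in the other. Random-effects logistic regression can ask whether that change differs by arm, provided arm is in the model. The plan treats them as interchangeable.

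If McNemar is chosen, the outcomes concerned get no randomised comparison. A shift over time that is common to both arms would give small p-values in either arm, or in one arm and not the other by chance. A reader could take that for an effect of IMR. Both arms receive active care over 9 to 21 months, so a shared trend in one direction or the other is plausible.

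**Working it through.** **1. The plan's own figure.** The only sample-size target is for GAF-F: difference 6, SD 15, power 0.8, alpha 0.05 (taken as two-sided). The normal approximation gives 99 per arm (198 in total). The t-based solution is 99.08, rounded up to 100 per arm, which is the stated total of 200. Power with 100 per arm is 0.807. The figure reproduces, and the present point does not bear on it.

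**2. What can be paired.** One control per experimental participant is an allocation ratio, not matching, because the arms are called independent and patients are allocated individually in permuted blocks. There are no matched pairs across arms. What remains is a patient's own values at two times.

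**3. What McNemar then tests.** Let *b* be the number who improve and *c* the number who worsen. The exact two-sided p-value is 2 × P(X ≤ min(*b*, *c*)), with X binomial(*b* + *c*, 0.5). Arm appears nowhere in it.

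**4. A worked example.** The rates are assumed, because the protocol gives none. In an arm of 100, a proportion falls from 40% to 25%, with *b* = 20 and *c* = 5.
- McNemar within that arm: 2 × P(X ≤ 5 | 25, 0.5) = 2 × 68,406 / 33,554,432 = 0.0041.
- If the other arm behaves identically, it also gives p = 0.0041.
- The comparison of arms at follow-up is 25/100 against 25/100, an odds ratio of (25/75)/(25/75) = 1. There is no treatment effect.

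**5. How often this would mislead.** Exact McNemar tests were simulated with 100 per arm, 20,000 trials, and the same probabilities of change in both arms, so that the true treatment effect is zero.

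| Improve / worsen (assumed, both arms) | Significant in IMR arm | Significant in IMR arm only | Significant, arms pooled |
|---|---|---|---|
| 20% / 5% | 83.5% | 13.6% | 99.2% |
| 15% / 5% | 54.7% | 24.6% | 87.5% |
| 10% / 10% | 3.0% | 2.9% | 3.5% |

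The third column follows from the second, since the arms are independent: 0.547 × (1 − 0.547) = 0.248, against 24.6% simulated. The test reacts to the time trend and not to the treatment. Without a trend it is rarely significant.

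**6. What the clause can reach.** GAF-F and the clinical-recovery measures are continuous, and so are the personal-recovery questionnaires. The candidates are therefore the items in Table 1 that are recorded repeatedly and could be dichotomised: alcohol and drug use, suicide attempts and employment. Substance abuse and suicide attempts are named secondary outcomes; employment is not in that list. The protocol does not say that any of them will be dichotomised.

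**The case against.** The strongest reply is that the sentence already contains the remedy. Its first part gives dichotomous outcomes logistic regression, which can carry an arm term at 9 and 21 months, and its second part offers random-effects logistic regression. A reader might infer that binary outcomes have no between-arm method at all. The text does not support that. What stands against the reply is that the sentence separates paired from other dichotomous outcomes, and for the paired ones it accepts McNemar as sufficient.

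A second reply is that nothing says McNemar will be run in each arm and the p-values set against each other. That is also true. Such a contrast is something a reader might fear, not something the plan announces, and describing change within an arm is a legitimate use of the test. But the plan does not label it as descriptive.

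A third tempting step is to say that regression to the mean will make both arms look improved. The documents do not support this. The eligibility criteria set no threshold of severity or poor functioning. They exclude large-scale substance abuse, so substance use might drift upwards instead. The point needs only a shared trend, in either direction.

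Finally, Power and sample size calls the secondary measures without a power calculation exploratory. A condensed article may also leave the list of paired variables to a fuller plan. Both limit the weight of the point. Neither repairs a stated option that cannot answer the trial's question.

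**Conclusion.** The point holds in a limited form. For paired dichotomous outcomes the plan permits a test with no arm term. If it is used alone, those outcomes get no comparison of IMR with treatment as usual, and a common time trend could be mistaken for an effect. Under the assumed rates with a trend, significance in the IMR arm alone would arise in about 14% to 25% of trials with no treatment effect, against about 3% without a trend. These percentages illustrate a property of the test and are not forecasts for this trial, because the protocol gives no binary rates and does not name the outcomes concerned.

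The weakness is confined to unspecified secondary binary items. The primary analysis, the continuous scales and the sample size are unaffected.

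**What to change.** Replace the second part of the sentence with a rule covering all binary outcomes:

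- The between-arm comparison of every dichotomous outcome at 9 and at 21 months is a logistic regression with an arm term.
- The model is adjusted for the baseline value of that outcome where it was collected, and for the stratification factors (diagnosis and centre), as far as the number of events allows.
- If the times are modelled jointly, use random-effects logistic regression and test the arm-by-time term.
- Drop the McNemar test, or keep it only as a description of change within an arm and say so.

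The cost is a change of wording. The strata are known at randomisation, and Table 1 already schedules the baseline values of alcohol and drug consumption, suicide attempts and employment. No new data, visits or participants are needed.
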